#### Control condition

Patients assigned to the control group will receive standard care only. In the standard care all patients visiting our pre-transplantation outpatient clinic receive a consultation with a transplant nephrologist, a transplant coordinator, and a social worker. Additional to this verbal information, the patients receive a variety of written educational material and a DVD regarding various living donation and transplantation programs. All materials are translated in the six afore mentioned foreign languages. They can study this material in the coming four weeks before their second visit to the outpatient clinic during which they have the opportunity to ask additional questions. Additionally, our patients are invited to attend 4–6 times a year informational meetings held in the various regional hospitals. The baseline and post-measurements will be either handed out by the educators during the hospital visit or sent via mail. If necessary the educators may help in completing the questionnaire. The questionnaires are also available in six languages.

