#### Experimental condition

The intervention consists of two sessions at the patient’s home. Session One: Firstly, at the beginning of the session the patient completes the baseline measurement. Secondly, the family network of the patients will be depicted on a genogram the educator in order to get familiar with the family structure and to recognize the values of that social system. The observation of the educators during the sessions represents an important source of information about how the present individuals relate to each other. In fact, the educators never rely solely on the individual’s verbal self-description to investigate social relations. Only by observing how the individuals behave with each other can the educators support or reject hypotheses based on self-reports. During this first session the educators watch for non-verbal clues that confirm or contradict what the social system is telling them. As the educators form tentative hypotheses about psychosocial hurdles, they do not offer advice or share their observations to avoid defensiveness. They rather focus on engagement by showing helpful interest while listening to the needs of the individuals and reinforcing the strengths of the respective social system. At the end of the first session the educators will make an inventory of individuals that the patient will invite for the second session. The educators may help in inviting identified individuals. The invitation will be conducted verbally accompanied by a brochure containing the 1) study purpose, 2) education content, and 3) contact information of the educators.

Session Two: The educators organize this session in such a way that they will do ‘what ever it takes’, in line with one of the basic principles of MST, to make this event as patient-tailored as possible. This means that the intervention will usually take place in the evenings and weekends since most friends and family members are working during office hours. The primary goal of this intervention is educational, therefore, it is not necessary that all the invitees are potential donors. The baseline-outcome measurement for the invitees will take place at the start of the second session. In exceptional cases multiple sessions are required in order to reach the goals set for those sessions. Table
1 shows the topics that will be discussed during the second session.

**Table 1 T1:** The educational topics discussed in the second session

		

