	1 Introduction	The purpose of the Kidney Team At Home-study
	2 Kidney disease	An introduction to kidneys and kidney diseases
	3 Dialysis	The various forms of dialysis
	4	Morbidity and mortality associated with dialysis
	5	The psychosocial consequences of a kidney disease and dialysis
	6	The advantages and disadvantages of dialysis compared to kidney transplantation
	7 Transplantation	The medical evaluation in preparation for donor nephrectomy and kidney transplantation
	8	The various programs of donation and transplantation (DDKT and LDKT)
	9	The number of DDKT and LDKT performed nationally and locally
	10	The differences in ethnicity regarding access to LDKT
	11	The differences in graft survival between DDKT and LDKT
	12 LDKT	Additional advantages and disadvantages of LDKT
	13	The risks and psychosocial aspects associated with donor nephrectomy
	14	The personal, emotional and financial aspects of LDKT for the recipient
	15 Discussions	Whether present individuals have considered donation of their kidney

During both sessions at the patients’ home we will use the therapeutic framework of MST in order to stimulate open communication between the patient and the family members and to use and profit of the strengths and possibilities of the natural network of the patient. The objective of MST is to achieve a lasting consensus on the patient’s goals and how these goals can be reached with engagement and/or support of his/her social ecology. Such long-term consensus can not be achieved if the interpersonal relations, personal autonomy and feelings of those involved are not sufficiently considered. Therefore, creating a ‘safe’ environment during the intervention is regarded as an important aspect of a successfully implemented intervention. The licensed psychologist who will be implementing this protocol is certified in practical systemic therapy. Both the psychologist and the transplant coordinator (educators) will be supervised by an official MST supervisor throughout the study period.

In order to minimize hurdles for participation interpreters are used when Dutch is not the primary language of those present. The interpreter will also help patients and invitees with questionnaires or understanding the informed consent if that may ease the transfer of information. At the end of the second session the patient and the invitees will receive the post-measurement. This questionnaire can be completed immediately or returned via the mail within a week. In Figure

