#### Primary outcome measures

##### Knowledge

Because there was no suitable instrument to measure knowledge on kidney diseases and all the possible RRT’s, we developed the Rotterdam Renal Knowledge-Test (RRK-T) based on Devin et al (1990), Stothers et al (2005) and Rodrigue et al (2007). The RRK-T consists on 30 true / false or multiple choice questions on kidney disease, dialysis and transplantation with a living or deceased donor [29]. For example, *‘Renal replacement therapy is necessary when the kidneys function for only 50%’.* A clinically significant change will be indicated by 8 points of difference compared to the baseline measurement and is additional to passing the clinical cut-off point of 17 points (each correctly answered questionnaire is awarded 1 point) [30].

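### The knowledge test, a primary outcome, is completed under conditions that differ by arm and occasion, so a change of completion mode can be counted as a change in knowledge

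*Protocol article*

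**What the plan says.** All references are to the protocol article, Methods and design.

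- **Instrument** (Primary outcome measures, Knowledge): "The RRK-T consists on 30 true / false or multiple choice questions on kidney disease, dialysis and transplantation". Each correct answer earns one point. On individual change: "A clinically significant change will be indicated by 8 points of difference compared to the baseline measurement", together with passing a cut-off of 17. The Objectives section names knowledge and communication in the primary research question.
- **Experimental arm, baseline** (Experimental condition, session one): "Firstly, at the beginning of the session the patient completes the baseline measurement".
- **Experimental arm, post-test** (same section): "At the end of the second session the patient and the invitees will receive the post-measurement". Then: "This questionnaire can be completed immediately or returned via the mail within a week".
- **Control arm, both occasions** (Control condition): "The baseline and post-measurements will be either handed out by the educators during the hospital visit or sent via mail". Educators may help with completion where needed.
- **Material held by patients** (Control condition): standard care includes written information and a DVD on living donation and transplantation programs. The experimental arm receives standard care as well.
- **Analysis** (Statistical analysis): the primary outcomes are analysed by mixed (multilevel) regression.

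**The concern.** The other primary scales ask about attitudes, perceived risk, intentions or how often people talk. The RRK-T is the one with correct answers, so it is the one whose score can rise because a form was filled in with help or reference material at hand.

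For experimental patients, the article fixes baseline completion at the session and then allows the post-test to be completed away from it. For controls, either form may be handed out or mailed, so the mode may be the same twice or may change in either direction. A change of mode within a patient cannot be told apart from learning, and the pattern of change is not the same in the two arms.

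The mixed model does not remove this. It handles repeated measures and data missing at random, whereas here the score itself is measured differently according to arm and time. At stake is whether the knowledge contrast, positive or null, can be read as an effect of the intervention.

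**Working it through.** **Completion conditions side by side**

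| | Baseline | Post-test |
|---|---|---|
| Experimental patients | At the start of session one | At once after session two, or mailed back within a week |
| Control patients | Handed out at the hospital visit, or mailed | Handed out at the hospital visit, or mailed |

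**How mode enters the contrast**

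Let g be the points a patient gains from unsupervised completion, and m the share of patients completing unsupervised. Taking the session as supervised, m is 0 at the experimental baseline. Then

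bias = g × [m(exp, post) − (m(control, post) − m(control, baseline))].

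The document gives none of g, the three shares, or a mean or SD for the RRK-T. It states no figure for this outcome that could be reproduced. The 78 per group was calculated for transplantation proportions whose values are not given, and is used below only as a sample size.

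**Sign, with an assumed g of 2 points**

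- m(exp, post) = 0.5, no change of mode in controls: 2 × (0.5 − 0) = +1.0 point.
- m(exp, post) = 0, half of controls change from supervised to mailed: 2 × (0 − 0.5) = −1.0 point.
- The same shift of 0.5 in both arms: 2 × (0.5 − 0.5) = 0.

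**Effect on the test, hypothetical values**

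Assume SD 5, baseline to post-test correlation 0.5, 78 per arm and no true effect.

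- SD of change = √(2 × 25 × (1 − 0.5)) = 5.
- SE = √(2/78 × 25) = 0.80.
- Rejection probability, two-sided 5%, is Φ(bias/SE − 1.96) + Φ(−bias/SE − 1.96).

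| Assumed share mailing × points (control mode unchanged) | Bias | Rejection under no true effect |
|---|---|---|
| 0.25 × 2 | 0.5 | 10% |
| 0.50 × 2 | 1.0 | 24% |
| 0.50 × 3 | 1.5 | 47% |

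With 80 per arm and an SD of change between 4 and 6, a net bias of 1 point gives 18% to 35%, and 2 points gives 56% to 89%.

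**How far the assumptions move the result**

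If 25% to 50% of experimental patients complete the post-test unsupervised, and each corrects 25% to 50% of the 13 to 17 items answered wrongly (baseline 17 to 13), the arm mean rises by 0.25 × 0.25 × 13 = 0.8 to 0.5 × 0.5 × 17 = 4.3 points. That is before any offset from controls.

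**Individual criterion**

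A patient starting at 13 reaches an 8-point change by correcting 8/17 = 47% of the wrong items (ending at 21). One starting at 15 needs 8/15 = 53% (ending at 23).

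**The case against.** The strongest reply is that the mechanism is possible but not documented. A reader might infer that look-up does occur and inflates the intervention effect. The document does not support that reading, for five reasons:

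- No passage reports look-up.
- The standard material is described as covering donation and transplantation programs, while the test also covers kidney disease and dialysis. Nothing says the material answers the items.
- The article does not say who decides whether a post-test is mailed, so it cannot be said that unsure patients would choose that route.
- For controls, the text describes how forms are distributed, not where they are completed.
- The experimental baseline normally takes place in the patient's own home and no closed-book rule is stated there, so calling it supervised is itself an inference from its place in the session.

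All of this stands, and it leaves the net sign undetermined.

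The magnitudes also rest wholly on assumed values. The Sample size calculation section expects a large knowledge effect, so a false-positive rate under no effect may not be the relevant scenario. That is fair, but the estimated size of a true effect would still be distorted. A mean shift of 0.5 to 1.5 points is also small beside the 8-point individual threshold, although one is a group mean and the other a criterion for a single patient.

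Two practical objections also stand. A ban on mailed forms could produce missing data that differ by arm, against the stated aim of minimising missing data. And in-person completion places educators who deliver the intervention beside the test.

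Finally, completion instructions and the recording of mode may be in a full protocol that is not shown, so their absence from an article is no fault. What remains is what the article does state: different arrangements by arm and occasion for a scored primary outcome.

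**Conclusion.** The concern holds as a weakness in measurement design. The RRK-T is completed under conditions that differ by arm and occasion, and the planned mixed model cannot remove a mode difference tied to both. A change of mode can be counted as a change in knowledge, and by different amounts in the two arms.

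The document does not allow the size or direction to be derived. The figures of 0.5 to 1.5 points, with false-positive rates of 10% to 47%, are hypothetical. They depend on the assumed mailing shares, look-up gain, SD and correlation, and on unchanged control mode. They show only that a modest net difference would matter at this sample size. Nothing here shows that a knowledge result would favour the intervention falsely. It could equally be understated, or the differences could cancel. The remedy is cheap enough that the change should be made without waiting for evidence of look-up.

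**What to change.** - **Same default mode.** Have the RRK-T completed in person on both occasions in both arms, without educational material and without help with the answers. Translation and help with reading can stay. Use the end of session two for the experimental post-test and the second outpatient visit already described under standard care for the control post-test.
- **Mail only as a fallback.** Keep it on identical terms in both arms, with the same return period and the same no-materials instruction, so that knowledge scores are not lost unequally.
- **Record** mode, place and date on each form.
- **Sensitivity analysis.** Report the knowledge contrast with mode taken into account. Label it supportive, because mode is determined after randomisation and a comparison restricted by it is no longer a randomised one.

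The cost is wording in the protocol and questionnaire instructions and a little more effort at contacts that already exist. Some mailed forms will remain, so the problem is reduced and made visible, not abolished. Educators will be present at more post-tests, which is why the rule against help with answers is needed. The sample size does not change.

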**Figure 1 F1:**
[figure not shown]
Design of the randomized controlled trial.

#### Primary outcome measures

##### Knowledge

Because there was no suitable instrument to measure knowledge on kidney diseases and all the possible RRT’s, we developed the Rotterdam Renal Knowledge-Test (RRK-T) based on Devin et al (1990), Stothers et al (2005) and Rodrigue et al (2007). The RRK-T consists on 30 true / false or multiple choice questions on kidney disease, dialysis and transplantation with a living or deceased donor [29]. For example, *‘Renal replacement therapy is necessary when the kidneys function for only 50%’.* A clinically significant change will be indicated by 8 points of difference compared to the baseline measurement and is additional to passing the clinical cut-off point of 17 points (each correctly answered questionnaire is awarded 1 point) [30].

##### Attitude

This is operationalized as the attitude that one has towards the discussion of RRT’s (for patients and invitees) and the acceptance (patients) or the donation (invitees) of a kidney (TPB) [26,31-33]. For example, *‘From my point of view discussing renal replacement therapy with my family and friends is pleasant / unpleasant’ and ‘I think that accepting a kidney from a living donor is good / bad.’* These were rated on a scale from 1–7.

##### Risk perception

The questionnaire structure is similar to other studies in which the PMT is used [34,35]. Negative and positive aspects of living kidney donation were rated on a 5-point scale (1 = not at all - 5 = a lot). For example, *‘I think discussing living kidney donation is emotionally burdensome’* and *‘I am afraid that in the future I could get a kidney disease from kidney donation.’*

##### Communication

Patients and invitees are asked if and how often they talk about kidney diseases and RRT with their family and friends. The development and selection of these questions was based on the validated ‘Family Functioning Questionnaire’ [36]. This questionnaire is designed to pinpoint the way families communicate and make choices regarding psycho-educational interventions. For example, ‘*How often have you recently talked with the people close to you about kidney transplantation from a living donor’ (1 = never - 5 = very often).*

##### Self-efficacy

We will measure the patients’ and invitees self-efficacy to communicate about LDKT. Participants could answer on a 5-point scale ranging from ‘I am able to … …’ to ‘I am not able to …’ [25,37,38]. For example, *‘I am able to discuss renal replacement therapies with my family and friends.’*

##### Subjective norm

Questions will be asked to determine if and how much patients and invitees value the thoughts of the other party regarding LDKT [37]. For example, *‘I value the opinion of people who are important to me’ (1 = not at all- 5 = very much).*

##### Intention

This factor measures the extent to which patients and invitees plan to / are willing to discuss RRT’s or if they would give or accept a kidney [25,26]. For example: *‘How much do you want to donate a kidney to the patient’ (1 = not at all - 5 = very much).*

#### Secondary outcome measures

Secondary outcomes are operationalized in terms of behaviour that may lead to LDKT or LDKT itself. This is divided into three categories: the number of applications for LDKT evaluation, the number of actual evaluations for LDKT, and the number of LDKT’s. These outcomes will be monitored using the patient’s medical records during the year following the intervention date. Furthermore, we will also monitor the timeframe between the intervention and the moment that the event arises (time-to-event).

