### Design & procedure

In this prospective RCT all patients will be invited to participate by the educators after the consultation with the transplant nephrologists. During the face-to-face informational consultation the patient will receive written and verbal information on the aims and procedures of the study. Spouses, relatives or friends accompanying the patient to the hospital may be present during this consultation. Our target is to include 80 patients of Dutch origin and 80 patients of non-Dutch origin in the study over a period of two years in order to compare effectiveness of the intervention among these two groups. With respect to the inequality in LDKT, patients of non-Dutch origin will inherently be overrepresented in the study. After informed consent is obtained, patients will be randomized to either the control or the experimental group. The control group will receive standard care. The experimental group will receive standard care plus a home-based educational intervention. In the face of the equity principle, we will provide all the study materials (e.g. brochures, questionnaires) in the six most common foreign languages in the Rotterdam municipality namely, English, Arabic, Turkish, Papiamento, Portuguese and Modern Hindi [29].

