#### Statistical analysis

Following the updated CONSORT statement [43], for this study the intention-to-treat population is defined as all randomized patients who are known to have received at least one home visit and who provide data for at least one post-baseline measurement for one or more of the key efficacy variables: no patient will be excluded for protocol violations which occurred during subsequent follow-up (modified intention-to-treat) [44]. Additional effort will be exerted by the educators to ask the drop-out patients to complete the post-measurement for the primary outcome.

For comparing the patients’ baseline-variables between the two research conditions the two tailed t-test for independent samples for the continuous variables, the two-tailed Mann–Whitney U-tests for the ordinal variables and the Chi-square tests for the categorical variables will be used. The effectiveness of our home-based educational intervention for the primary outcome variables will be analyzed with mixed modeling, i.e. multilevel regression modeling. The additional value of this multilevel testing lies in the flexibility to model individual growth trajectories and to handle missing data. The latter will only hold if structure of the missing data is Missing Completely At Random (MCAR) or Missing At Random (MAR), but not if the data turns out to be Missing Not At Random (MNAR). This technique is appropriate since missing data and drop-outs are inevitable in longitudinal research. Moreover, missing data affects study power simply by the reduced availability of data points [45]. We will strive to firstly minimize missing data, and to subsequently take this into account during analysis. The methodology of mixed modeling for repeated measures allows us the use of flexible error variance-covariance structure. Additionally, the predictive value of the baseline-parameters (main-outcome variables) on effectiveness can be estimated.

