Finally, semiparametric regression analysis will be employed using Cox Proportional Hazard Model to examine the significance of the contingency between the hazard for an event of the experimental and control group on the secondary outcome variables. This model enriches the analysis by incorporating covariates in the regression equation (e.g. age, gender, ethnicity, dialysis time). Time-to-event graphs will be depicted for the experimental and control group separately. Patients with a LDKT will be regarded as having the ‘event’ whereas patients who continue dialysis during the follow-up period will be censored. DDKT is modeled as a competing event and therefore patients who take-up this treatment will also be censored.

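### One-year follow-up and time-to-event for the secondary outcomes start at an intervention date that controls do not have, so the Cox comparison has no common time origin

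*Protocol article*

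**What the plan says.** Under Secondary outcome measures, the protocol article follows three outcomes (LDKT applications, evaluations and transplants) through the medical record "during the year following the intervention date". The time-to-event variable is "the timeframe between the intervention and the moment that the event arises (time-to-event". Both clocks therefore start at the intervention.

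Under Control condition: "Patients assigned to the control group will receive standard care only". No section gives controls an index date, matched date or assigned pseudo-intervention date.

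Under Design & procedure: "After informed consent is obtained, patients will be randomized to either the control or the experimental group". The home sessions come after that. Under Experimental condition, "The intervention consists of two sessions at the" patient's home, and "In exceptional cases multiple sessions are required in order to reach the goals set for those sessions". Which of these sessions supplies the intervention date is not stated.

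Under Statistical analysis, a Cox model compares "the hazard for an event of the experimental and control group" on the secondary outcomes, with time-to-event graphs for each arm. The analysis population is "all randomized patients who are known to have received at least one home visit", with at least one post-baseline measurement, so it does not bring randomisation back as the starting point.

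**The concern.** A randomised time-to-event comparison needs one time origin that exists in both arms and is not itself a consequence of allocation. The stated origin fails on both counts: it is undefined for controls and falls after randomisation for experimental patients. Whoever runs the analysis must invent a control date.

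If that date is randomisation or the clinic visit, both windows last 12 months but the experimental one lies later by the time taken to arrange the sessions. An application, evaluation or transplant between randomisation and the session would count in a control patient and not in an experimental one. Where the event rate changes with time since referral, the shift alone can produce a difference between arms.

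These outcomes answer the second research question, on inequality in the pursuit of LDKT, and the sample size calculation is based on the LDKT proportion.

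**Working it through.** **What can be reproduced.** The plan attaches no figure to this point. The nearest is the 78 patients per group in Sample size calculation, which rests on two LDKT proportions that the article does not give, so it cannot be reproduced. Pairs such as 10% v 29% or 20% v 42% are consistent with 78 (continuity-corrected, power 0.80, two-sided alpha 0.05). The calculations below do not bear on that figure.

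**Common set-up.** There is no treatment effect. The control clock runs from 0 to 12 months after randomisation (an assumption, since the article states no control origin). The experimental clock runs from d to d + 12 months, among patients event-free at d. The delay d is not in the article; 1, 2 and 3 months are assumed.

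**A. Constant hazard from randomisation.** The cumulative hazard over any 12 months is the same, so the ratio is 1.00 and the one-year risk is equal in both arms. With an assumed one-year risk of 30%, the share of experimental patients with an event before the session is 1 − 0.7^(d/12) = 2.9%, 5.8% and 8.5% for d = 1, 2, 3. These events fall outside the window, but the window ends d months later, so the comparison among patients event-free at d is unbiased. If those early patients stayed in the denominator with their events uncounted, the experimental proportion would be 29.1%, 28.3% and 27.4% against 30%, a small loss for the experimental arm.

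**B. Three-month event-free lag, then constant hazard.** The lag and a 30% control risk at 12 months are assumed.
- Monthly hazard = −ln(0.7)/(12 − 3) = 0.3567/9 = 0.0396.
- Experimental time at risk = 12 + d − max(3, d) = 10, 11, 12 months.
- Experimental risk = 1 − exp(−0.0396 × time) = 32.7%, 35.3%, 37.8%.
- Risk ratio against 30% = 1.09, 1.18, 1.26.

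**C. Weibull hazard with shape k.** The ratio of cumulative hazards over the two windows, a rough guide to the hazard ratio, is [(12 + d)^k − d^k] / 12^k.

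| Shape k (assumed) | d = 1 | d = 2 | d = 3 |
|---|---|---|---|
| 0.5 (falling) | 0.75 | 0.67 | 0.62 |
| 1 (constant) | 1.00 | 1.00 | 1.00 |
| 1.5 (rising) | 1.10 | 1.19 | 1.27 |
| 2 (rising) | 1.17 | 1.33 | 1.50 |

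For k = 2 and d = 3 this is (225 − 9)/144 = 1.50. For k = 0.5 and d = 3 it is (3.873 − 1.732)/3.464 = 0.62.

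**False-positive rate.** This uses a two-sided normal approximation for two proportions, 80 per arm (160 patients, 1:1 assumed) and a one-year control risk of 20% (assumed). The experimental risk is 1 − 0.8^ratio, with the ratio from the table; z is the difference in risks divided by its standard error; the rejection probability is 1 − Φ(1.96 − z) + Φ(−1.96 − z).
- k = 1: 0.050 at every delay.
- k = 1.5: 0.059, 0.081, 0.111.
- k = 2: 0.074, 0.139, 0.240.

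**After the fix.** With time zero at randomisation and the same 12 months in both arms, the null ratio is 1.00 and the rejection probability is 0.05 for every shape and delay.

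**The case against.** The strongest reply is that the article never says when the control clock starts. The offset is therefore unknown and could be close to zero. Controls complete baseline and post-measurements, and experimental patients complete the baseline at Session One, so a baseline-anchored or matched control date could bring the arms close together. The design figure is not shown and may carry a timeline. This stands against two inferences that a reader might draw: that the arms are certain to be observed over different windows, and that every possible control date must differ from the experimental clock. The text supports neither. It remains true that the text describes no such date, and the baseline is taken differently in the two arms: at the hospital or by mail for controls, at home for experimental patients.

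A reader might also call this immortal time bias. The label does not fit. Waiting time before the session is left out of the experimental clock rather than counted as exposed, event-free follow-up. The problem is a delayed origin.

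A third tempting inference is that the shift favours the intervention. That needs a rising hazard. The eligibility rule that no potential living donor is yet available makes a slow start plausible, mainly for transplants. But patients already on the wait list are enrolled too, and applications could come soon after the consultation. The direction may differ between the three outcomes.

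Finally, these outcomes are secondary. The primary questionnaire outcomes do not use this clock. That is correct and limits the severity.

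**Conclusion.** The defect holds as a badly fixed definition. The stated origin is undefined in one arm and post-randomisation in the other, so the rule cannot be applied to controls as written and gives the Cox model no common starting point. This is not detail left to an analysis plan: a plan would have to override the stated origin or invent a control date.

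The size and direction of any bias cannot be settled from the document. If controls are followed from randomisation, a constant hazard gives none in the hazard ratio or the one-year proportion. A rising hazard favours the experimental arm; null risk ratios of about 1.09 to 1.26 illustrate this, but they rest on assumed delays of 1 to 3 months, an assumed three-month lag and an assumed 30% control risk. A falling hazard reverses the sign. The 3% to 9% of experimental patients with uncounted early events under a constant hazard should not be read as bias in the comparison, because the later end of the window offsets them.

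This should be fixed, because it touches the second research question and the outcome used for sample size. It does not threaten the primary analysis.

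**What to change.** Set time zero at the date of randomisation in both arms, for the record review and for the Cox model alike. Review every randomised patient's medical record for the same fixed period from that date: 12 months, or 12 months plus the maximum time allowed for scheduling the sessions. Count applications, evaluations and transplants that occur before the home visit. Report time from a named session (for example Session Two) only descriptively, within the experimental arm.

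The cost is a change of wording. The data already come from medical records and no sample size figure changes. The experimental arm has a slightly shorter observation period after the session, or the record review is extended by a few weeks in both arms.
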